### Outcome measures

The primary outcome measure is the Patient Health Questionnaire-9 (PHQ-9) [37], a reliable and valid 9-item measure of depression that has been used widely with advanced cancer patients [38]. This brief measure is a subscale of the Patient Health Questionnaire (PHQ), a patient self-report version of the Primary Care Evaluation of Mental Disorders (PRIME-MD), a widely used tool to screen for mental health disorders in primary care [39]. Two additional questions on the PHQ-9 include: question 9a which assesses suicidal intent if a patient endorses suicidal ideation (i.e., “Is there a chance you would do something to end your life?” Yes/No); and question 10 which assesses functional impairment (i.e., “How difficult have these problems made it for you to do your work, take care of things at home, or get along with other people?” Not difficult at all/Somewhat difficult/Very difficult/Extremely difficult).

The secondary outcome measures assess domains hypothesized to respond directly or indirectly to the intervention through its potential impact on communication with health care providers, shifts in personal relationships or other factors. A portion of the Mood Disorders and Optional Disorders Module from the Structured Clinical Interview for *Diagnostic and Statistical Manual of Mental Disorders* (DSM) (SCID) [40] (SCID-1 Research Version for DSM-IV-TR Axis 1 Disorders, January 2010) is administered in this study. The SCID is a semi-structured interview that allows researchers to make diagnoses of major and minor depression consistent with DSM diagnostic criteria [41].

The Generalized Anxiety Disorder-7 (GAD-7) [42] is a widely used and validated 7-item self-report measure designed to screen and assess the frequency of GAD symptoms. It is a subscale of the PRIME-MD [39]. An eighth item, rating how difficult these symptoms have made it to do work, take care of things at home, or get along with other people, has been included.

The Functional Assessment of Chronic Illness Therapy-Spiritual Well-being Scale (FACIT-Sp) [43] is a 12-item self-report measure of spiritual well-being, assessing the sense of meaning, peace and faith, that has been widely used in palliative care research [44, 45].

The Posttraumatic Growth Inventory (PTGI) [46–48], a 21-item self-report scale that measures positive psychological changes after trauma, has been used as a measure of psychological growth in response to the psychological trauma of cancer [49] and as an outcome measure for intervention studies [50, 51]. The PTGI provides a total score based on the experience of new possibilities and spiritual change, growth in personal strength, relations with others, and appreciation of life.

The Quality of Life at the End of Life-Cancer Scale (QUAL-EC) [52] is a measure of quality of life in patient populations near the end of life. We omitted the symptom control subscale, thereby reducing this self-report measure to 14 items.

Death anxiety is assessed using the 15-item Death and Dying Distress Scale (DADDS), which we have developed for use in advanced cancer [53]. Unlike other death anxiety measures (e.g., [54]), the DADDS is designed for populations facing imminent death. It addresses fears about the dying process, and about lost opportunities and self-perceived burden placed on others as a result of impending mortality.

The Demoralization Scale (DS) [55] is a 24-item self-report measure that assesses loss of meaning and purpose, disheartenment, and helplessness.

Attachment security is assessed using the 16-item modified Experiences in Close Relationships Inventory (ECR-M16) [56], tailored for use with advanced cancer patients. It assesses attachment avoidance (i.e., discomfort with closeness and discomfort depending on others) and attachment anxiety (i.e., fear of rejection or abandonment).

Participants who are married, common-law, or in a long-term relationship will be asked to complete the ten-item Couple Communication Scale (CCS) [57], which is concerned with an individual’s feelings, beliefs, and attitudes about the communication in his/her relationship; the CCS is taken from the PREPARE/ENRICH Inventory [57].

Lastly, the Clinical Evaluation Questionnaire (CEQ) is a seven-item measure that we have newly developed to assess the extent to which individuals feel emotionally supported by clinical services in the domains relevant to CALM therapy. For intervention participants, the CEQ refers to the patients’ experience of CALM therapy. For control participants, the CEQ refers to the patient’s interactions with the health care team at the Princess Margaret. The CEQ is assessed only at 3 and 6 months. See Additional file 1 for this measure.

Additional data collected will include: demographics, medical and psychiatric history, performance status, and disease-related symptom severity. Performance status is rated by research staff with patient input at all study time points using the Karnofsky Performance Status (KPS) scale [58]. A shortened version of the Memorial Symptom Assessment Scale (MSAS) [59] is used to measure the presence and severity of 28 common physical symptoms of cancer.

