**Methods/Design:**

The study is an unblinded randomized controlled trial with 2 conditions (intervention plus usual care versus usual care alone) and assessments at baseline, 3 and 6 months. The site is the Princess Margaret Cancer Centre, part of the University Health Network, in Toronto, Canada. Eligibility criteria include: ≥ 18 years of age; English fluency; no cognitive impairment; and diagnosis of advanced cancer. The 3–6 session intervention is manualized and allows for flexibility to meet individual patients’ needs. It is delivered over a 3–6 month period and provides reflective space for patients (and their primary caregivers) to address 4 main domains: symptom management and communication with health care providers; changes in self and relations with close others; sense of meaning and purpose; and the future and mortality. Usual care at the Princess Margaret Cancer Centre includes distress screening and referral as required to in-hospital psychosocial and palliative care services. The primary outcome is frequency of depressive symptoms and the primary endpoint is at 3 months. Secondary outcomes include diagnosis of major or minor depression, generalized anxiety, death anxiety, spiritual well-being, quality of life, demoralization, attachment security, posttraumatic growth, communication with partners, and satisfaction with clinical interactions.

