### Proposed analyses

Analyses will be by intention to treat. ANCOVA will be used to test for outcome differences between experimental and control groups at follow-up, controlling for baseline scores and covariates, specifically age, gender and symptom burden from disease. Sensitivity analyses, including complete case analysis and multiple imputation, will be conducted to assess the impact of missing values. Linear mixed effects modeling will be used to test for group differences in trajectory over time. Intervention participants are expected to show greater benefit (i.e., less distress or greater well-being) over time relative to control participants. Structural equation modeling and factor analysis may also be used to study treatment effects on combined or composite outcomes.

The outcome of death anxiety may require special consideration, since death anxiety scores at baseline in the very low range can represent minimization or non-reflectiveness about such concerns (unpublished observations). Non-reflective individuals may increase in death anxiety as their disease progresses and as avoidant psychological strategies become less effective with physical decline. Analyses will, therefore, examine the effect of removing individuals with low death anxiety scores at baseline (i.e., DADDS < 15). Effective psychotherapeutic intervention may actually be associated with increased death anxiety due to the processing of such concerns, thereby weakening the power to detect significant treatment effects.

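### The CEQ asks the two arms about different things, so its between-arm difference mixes any effect of CALM with a change in what is being rated

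*Protocol article*

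**What the plan says.** All references are to the protocol article.

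- **Status.** The abstract's list of secondary outcomes ends with "communication with partners, and satisfaction with clinical interactions". The Outcome measures section introduces the secondary instruments with "The secondary outcome measures assess domains hypothesized to respond directly or indirectly to the intervention" and describes the CEQ as the last of them.
- **Construct.** The CEQ is a newly developed seven-item measure meant to "assess the extent to which individuals feel emotionally supported by clinical services in the domains relevant to CALM therapy".
- **Referent, intervention arm.** "For intervention participants, the CEQ refers to the patients’ experience of CALM therapy".
- **Referent, control arm.** "For control participants, the CEQ refers to the patient’s interactions with the health care team at the Princess Margaret".
- **Timing.** "The CEQ is assessed only at 3 and 6 months".
- **Analysis.** The Proposed analyses section is by intention to treat and states that "ANCOVA will be used to test for outcome differences between experimental and control groups at follow-up, controlling for baseline scores and covariates". It does not name the CEQ and exempts no secondary measure from the between-arm comparison. Nothing elsewhere restricts the CEQ to descriptive or within-arm use.

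**The concern.** A between-arm difference estimates a treatment effect when the same outcome is measured in the same way in both arms. Here the intervention arm scores a psychotherapy built around the domains that the CEQ covers, and the control arm scores its dealings with the clinical team at the centre. Treatment and referent change together for every participant.

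The construct is felt support from clinical services. A reader who sees a higher CEQ score in the CALM arm will naturally conclude that adding CALM makes patients feel better supported. The design cannot show that, because intervention participants are never asked about the care that both arms share. The Discussion says that the investigators attach great weight to the secondary measures, so a favourable CEQ result could well be cited as evidence of benefit.

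**Working it through.** **1. What the contrast contains.** Let T(1) and T(0) be the mean rating of the health care team if patients are assigned to CALM plus usual care or to usual care alone. Let K(1) be the mean rating of CALM among those assigned to it. The planned comparison is K(1) − T(0), which splits as

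K(1) − T(0) = [T(1) − T(0)] + [K(1) − T(1)].

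The first bracket is a treatment effect on a common referent. The second is the difference between rating CALM and rating the team in the same patients. T(1) is not collected, so neither bracket can be estimated alone, and baseline or covariate adjustment does not help. T(1) could have been asked: the Trial conditions section gives the intervention arm usual care plus CALM, so both arms deal with the same team.

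**2. The plan's own figures.** No stated figure depends on the CEQ. The recalculated sample size, which concerns depression scores, serves only to set the scale. With r = 0.50 and d = 0.405,

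n = 2(1.96 + 0.842)²(1 − 0.50²)/0.405² + 1 = 2(7.851)(0.75)/0.1640 + 1 = 72.8, so 73 per group at study end;

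73 × (1/0.75) × (1/0.90²) = 120.2, so 121 per group at baseline.

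Both agree with the article. Completers per arm would be about 121 × 0.75 = 90.75; 90 is used below.

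**3. Illustration with assumed shifts.** The documents give no CEQ data, so the shift s (in SD units) is an assumption. Suppose CALM has no effect on felt support, so the first bracket is zero, and the referent alone moves the mean by s. For an unadjusted two-sided 5% z-test, SE = √(2/90) = 0.149 and

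P(significant) = 1 − Φ(1.96 − s/SE) + Φ(−1.96 − s/SE).

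| Assumed s (SD) | P(significant) |
|---|---|
| 0 | 0.050 |
| 0.1 | 0.103 |
| 0.2 | 0.269 |
| 0.3 | 0.521 |
| 0.4 | 0.765 |
| 0.5 | 0.918 |

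The formula is symmetric in s, so a shift against CALM of the same size has the same probability of giving a significant result in the other direction. The table shows how sensitive the test is to the referent. It is not evidence that a shift of any given size exists.

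**4. Two minor notes.**
- With no baseline CEQ, an ANCOVA that adjusts for the baseline score does not apply to this measure.
- An intervention participant who attends no session has no CALM experience to rate. The article defines non-compliance as fewer than three sessions and reports 90% compliance at the recalculation. About 10% (0.10 × 121 ≈ 12 per arm at the planned size) therefore fall below three. How many of these had none is not stated; the range is 0 to about 12.

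**The case against.** The strongest reply is that the choice is disclosed in plain words, that the CEQ is the last of many secondary measures, and that no CEQ-specific test or claim is written down. An unseen analysis plan might already treat it descriptively. This limits the weight of the point but does not remove it. The differing referents are fixed by the instrument as the article describes it, and the general analysis sentence covers outcomes without exception.

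Several stronger readings are tempting, and the objection to each of them stands:

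- **That a difference in favour of CALM is built in.** A reader might infer this from the picture of a dedicated therapist set against routine clinic contact. The article describes usual care as including distress screening and possible referral to social work, psychiatry, psychology or palliative care, with about a third of metastatic patients referred for psychosocial care. Controls may thus be rating psychosocial clinicians too. They also rate all of the team's support, while intervention participants rate CALM only. The shift could run either way.
- **That an intention-to-treat analysis of the CEQ is impossible.** The difficulty touches only participants with no sessions, an unknown part of roughly 10% of the arm. The plan includes sensitivity analyses for missing values, and the item wording is in an additional file that is not shown.
- **That the missing baseline is an error in its own right.** The article states the timing openly. Dropping the baseline term for a measure taken only at follow-up is detail that an analysis plan would settle.

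**Conclusion.** The point holds for the referent. If the plan is followed as written, the between-arm CEQ comparisons at 3 and 6 months cannot be read as an effect of CALM on felt support, because treatment and the object rated are completely confounded. This rests on the referents stated in the Outcome measures section and on the absence of any common-referent version in the article. It needs no assumption about CEQ scores.

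The direction and size of the bias are unknown. A shift in favour of CALM is plausible, since the items cover CALM's own domains, but the documents do not establish it. The damage is confined to one secondary outcome. The PHQ-9 primary analysis, the sample size and the other secondary measures are unaffected. The matter should be settled before the CEQ is analysed.

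**What to change.** In the Proposed analyses section, or in the analysis plan if that is where secondary outcomes are specified, exempt the CEQ from the between-arm secondary efficacy tests. Report it descriptively within each arm as a measure of acceptability or process. Wherever the two arms' scores appear together, state that intervention participants rated CALM and controls rated the health care team. Report how many intervention participants attended no session and how their CEQ forms were handled.

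The cost is a short change of wording and the loss of one nominal secondary comparison.

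A single stem for both arms would permit a genuine comparison, but it is not a cheap alternative at this stage. By the February 2014 recalculation 112 participants already had baseline and 6-month depression scores, so a new stem would reach only those remaining. It would also change an instrument in mid-trial, and the forms already collected could not be pooled with the new ones.

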### Initial power calculations

Although the primary endpoint was designated at 3 months, sample size calculations took into account the secondary 6-month endpoint in order to sufficiently power the trial to examine outcomes at study end. We used the following sample size formula for an analysis of covariance (ANCOVA) design in which two groups are compared at follow-up, controlling for baseline scores [60]:$$ \mathrm{n} = \left[2{\left({\mathrm{Z}}_{\mathrm{A}} + {\mathrm{Z}}_{\mathrm{B}}\right)}^2\left(1\ \hbox{--}\ {\mathrm{r}}^2\right)/{\mathrm{d}}^2\right] + 1 $$where d = (X̅_1_ – X̅_2_)/SD, i.e., Cohen’s d [61];

n = sample size per treatment group required at follow-up;

Z_A_ = 1.96, the z-score associated with a two tailed test at alpha 0.05;

Z_B_ = 0.842, the z-score associated with a desired power of 0.80; and

r = correlation between measurements at baseline and study end.

Based on this longitudinal study: [61] (CIHR #MOP 62861) of metastatic gastrointestinal and lung cancer patients [1, 2], we observed a correlation of 0.72, n = 137, between depression scores at baseline and 6 months. We used 0.70 as our estimate of r. We planned to detect d = 0.405, a small to medium sized effect [61], consistent with prior work [9, 62].

Substituting these values into the equation results in:$$ \mathrm{n} = \left[2{\left(1.96+0.842\right)}^2\left(1\hbox{--} 0.7{0}^2\right)/0.40{5}^2\right]+1=\left[2(7.851)(0.51)/(0.164)\right]+1=49.8 \sim 50 $$

A minimum of 50 participants per group was initially required at study end.

The following formula was used to adjust for attrition and non-compliance with intervention (i.e., having less than three CALM sessions) [63, 64]:$$ {\mathrm{n}}_{\mathrm{b}} = {\mathrm{n}}_{\mathrm{e}}\left(1/\mathrm{p}\right)\ \left(1/{\mathrm{c}}^2\right) $$where n_b_ = sample size required at baseline per treatment group;

n_e_ = sample size required at endpoint per treatment group;

p = proportion of participants who will reach study end; and

c = proportion of participants compliant with intervention.

We initially estimated a trial completion rate of 60 % and compliance rate of 80 % based on prior research [38]. Substituting relevant values into the equation results in:$$ {\mathrm{n}}_{\mathrm{b}}=50\left(1/0.60\right)\left(1/0.8{0}^2\right)=50(1.667)(1.563)=130.3 \sim 131 $$

Therefore, 131 participants per group or 262 total participants will be required at baseline. Based on previous experience [1, 2], trial recruitment was anticipated to last 4.5 years.

### Sample size recalculation

A sample size recalculation was conducted in February 2014 in light of observed differences from initial estimates in rates of attrition and compliance. This procedure was undertaken with no awareness or examination of treatment effects. The observed correlation between depression scores at baseline and 6 months was 0.50, n = 112. To detect an effect size of 0.405 with a 2-tailed test, the required n per group is 73 at study end. Approximately 75 % of participants had reached study end at 6 months and 90 % of participants were compliant with intervention. Adjusting for these factors, a minimum of 121 participants per group or 242 participants overall will be required at baseline. Note that contamination of control participants (i.e., having two or more sessions with a CALM-trained therapist) was negligible and was not adjusted for.

### Proposed analyses

Analyses will be by intention to treat. ANCOVA will be used to test for outcome differences between experimental and control groups at follow-up, controlling for baseline scores and covariates, specifically age, gender and symptom burden from disease. Sensitivity analyses, including complete case analysis and multiple imputation, will be conducted to assess the impact of missing values. Linear mixed effects modeling will be used to test for group differences in trajectory over time. Intervention participants are expected to show greater benefit (i.e., less distress or greater well-being) over time relative to control participants. Structural equation modeling and factor analysis may also be used to study treatment effects on combined or composite outcomes.

The outcome of death anxiety may require special consideration, since death anxiety scores at baseline in the very low range can represent minimization or non-reflectiveness about such concerns (unpublished observations). Non-reflective individuals may increase in death anxiety as their disease progresses and as avoidant psychological strategies become less effective with physical decline. Analyses will, therefore, examine the effect of removing individuals with low death anxiety scores at baseline (i.e., DADDS < 15). Effective psychotherapeutic intervention may actually be associated with increased death anxiety due to the processing of such concerns, thereby weakening the power to detect significant treatment effects.

## Discussion

CALM therapy is a novel psychotherapeutic intervention that we have developed to alleviate distress and to promote psychological growth and well-being in patients with advanced or metastatic cancer. Unique features of this supportive-expressive therapy include its theoretical foundation in relational, attachment and existential theory, its tailored focus on the problems of advanced cancer, the inclusion of primary informal caregivers in one or more sessions of the intervention, and the potential for recruitment of participants from a clinic-based population. Although depression is specified as the primary outcome, we also place great importance on the secondary outcome measures, which we believe are highly relevant to the problem of advanced cancer and may be improved by the intervention.

There are particular challenges in an RCT of this kind. These include the identification of participants motivated to engage in psychotherapy at the time of recruitment, recruitment and retention of patients with advanced illness, and the possibility that outcomes will be affected by dramatic changes in clinical status that may occur during the course of advanced cancer. The clinic-based recruitment strategy is facilitated by the engagement of the research team with the oncology clinic staff. This clinic-based approach will be of great value to inform our understanding of the benefit of CALM in both depressed and non-depressed individuals who were not necessarily seeking professional psychosocial care.

We are fortunate to have recruited a group of committed and experienced psychosocial clinicians, who have been intensively trained and supervised to deliver the CALM intervention. Preliminary qualitative [4] and quantitative pilot studies [65] have provided support for the feasibility and value of CALM therapy, but the large phase III RCT described here will provide a more definitive assessment of its potential efficacy. Such evidence will determine whether it can be justified to routinely incorporate CALM into the comprehensive care of patients with advanced cancer.

## Trial status

The trial is currently underway. Trial Registration: ClinicalTrials.gov NCT01506492.

## Abbreviations

ANCOVA: analysis of covariance
CALM: Managing Cancer And Living Meaningfully
CCS: Couple Communication Scale
CEQ: Clinical Evaluation Questionnaire
DADDS: Death and Dying Distress Scale
DART: Distress Assessment and Response Tool
DS: Demoralization Scale
DSM: *Diagnostic and Statistical Manual of Mental Disorders*
ECR-M16: 16-item modified Experiences in Close Relationships Inventory
FACIT-Sp: Functional Assessment of Chronic Illness Therapy-Spiritual Well-being Scale
GAD-7: Generalized Anxiety Disorder-7
KPS: Karnofsky Performance Status
MSAS: Memorial Symptom Assessment Scale
PHQ: Patient Health Questionnaire
PHQ-9: Patient Health Questionnaire-9
PRIME-MD: Primary Care Evaluation of Mental Disorders
PTGI: Posttraumatic Growth Inventory
QUAL-EC: Quality of Life at the End of Life-Cancer Scale
RCT: randomized controlled trial
REB: Research Ethics Board
SCID: Structured Clinical Interview for DSM Diagnoses
SOMC: Short Orientation-Memory-Concentration test
UHN: University Health Network
